#### 11.4 Brain Magnetic Resonance Imaging (MRI) Scans.

If the participant is in the sub-group for MRI brain imaging, these will be performed at the NNUH by [name] (Radiology Consultant) or a member of his team. The analysis of this data will be performed by [name] following standard protocols.

Scans will be performed to allow for the cognitive and behavioural data collected at the previous visits to be related to neuroanatomical changes. The 60-minute scan will capture both structural and functional sequences.

Information regarding the safety and comfort relating to MRI scanning will be provided in the PIS, and participants will have the option to consent to this component of the study in the Informed Consent Form. If participants elect to undergo the MRI scan, they will be screened prior to scanning for any metal in the

body or other contraindications to scanning, including claustrophobia (this element is included in the Pre-Study Visit Checklist).

The scanning procedure will involve participants having their head scanned within the MRI machine. They will be provided with earplugs and additional ear protection from the noise of the scanner, as well as pillows, foam padding, and blankets to ensure comfort during the scan. They will be provided with a button to alert MRI staff of any complications or discomfort during the scan, and the scan will be aborted immediately at any time if the participant wishes. There are no known adverse side effects with having a single or multiple MRI scans of any length, even repeated scans after short intervals provided that the participant does not have any metal within or on the body. The MRI scans do not involve injection of radioactive compounds or exposure to potentially harmful radiation.

It is possible that during testing unexpected abnormalities may be found that may require further medical attention. For example, an 'incidental' finding of a brain tumour on MRI scanning or any other risks beyond the scope of the study. This is unlikely as the participants are considered healthy at the time of the study. However, in the event of this happening the participant will be informed and with their consent, their GP who will be asked to take further action as they see necessary. Participants will also consent to having their GP informed of any relevant information, including information raising concerns about their wellbeing, before they commence participation in the study. Participants can opt out for personal or medical reasons and this will not affect their ability to continue in the study. Any findings following MRI scanning will follow the NNUH Trust policy.

#### 11.4.1 MRI Analysis

The 3D T1-weighted sequences will be acquired as follows: coronal orientation, matrix 256 \_ 256, 200 slices, 1 x 1 mm in-plane resolution, slice thickness 1 mm, TE/TR = 2.6/5.8 msec. 3D T1-weighted sequences will be analysed using FSL and SPM software packages. Following brain extraction, tissue segmentation will be carried out using FMRIB's Automatic Segmentation Tool (FAST). The resulting grey matter partial volume maps will be aligned to the Montreal Neurological Institute standard space (MNI52) using the nonlinear registration approach with FNIRT which uses a b-spline representation of the registration warp field. To correct for local expansion or contraction, the registered partial volume maps will be modulated by dividing them by the Jacobian of the warp field. The Jacobian modulation step will

not include the affine part of the registration, which means that the data will be normalized for head size as a scaling effect. The modulated images will be then smoothed with an isotropic Gaussian kernel with a standard deviation of 3 mm (FWHM: 8 mm). This will be followed by GLM and Bayesian statistics on a regional and whole brain level.

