#### 5.2.2 Subgroup 2 – Brain Magnetic Resonance Imaging (MRI) Scans.

30 participants from the high-risk cohort will form subgroup 2 and will undergo MRI-based brain imaging on two occasions (at the beginning and end of the study) at the NNUH Imaging Department. Imaging protocols will adopt the same design and concept as the Alzheimer's Disease Neuroimaging Initiative 2 (ADNI2) protocol (ClinicalTrials.gov Identifier: NCT01231971) to measure the progression of MCI (1h total scanning time). The sequence protocol for the MRI will involve structural and functional sequences, which are established on the NNUH MRI scanner by [name] and commonly used in his dementia cohorts. Structural sequences will allow measurement of grey and white matter integrity in participants, whereas functional sequences will allow measurement of brain connectivity and perfusion changes. We hypothesize that medial temporal structures will be intact in low risk participants but those in the medium risk group might already show subtle structural and functional changes.

MCI can be a very emotive subject and the researchers do not wish to cause participants any undue stress or anxiety. For this reason, participants will not be made aware of the 3 cohorts, but will be told that out of 360 participants, 30 will be offered a brain MRI scan based on the result of their Pre-Study Visit test results (mini-ACE and CCI). They will also be reassured that the test result, in combination with being offered the MRI scan, is not indicative of any clinical diagnosis and is purely for the purposes of this research study. The brain MRI scans are optional and does not affect participation in the study.

Each consecutive participant who is enrolled in to cohort 3 will be offered the brain MRI scan. If the participant declines this or is not medically able to have the scan, it will be offered to the next consecutive participant until the required number of 30 is achieved. This group will form subgroup 2.

At the point of consenting at the Pre-Study Visit, the Study Researcher will not know which cohort the participant will be placed in and will therefore ascertain eligibility and personal preference for imaging for all enrolled participants for consistency by using the Pre-Study Visit Check-list (Annex 9).

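### The MRI modulation rule in Section 11.4.1 is cross-sectional: used on two scans per person it can take part of any brain-wide shrinkage out of the within-person change

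*Protocol*

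**What the plan says.** Section 5.2.2 of the Protocol forms subgroup 2 from 30 high-risk (cohort 3) participants. Each is scanned twice, near the Baseline Visit and shortly before Study Visit 8 at 48 months. The stated purpose is "to measure the progression of MCI". Section 11.4 adds that the scans allow "cognitive and behavioural data collected at the previous visits to be related to neuroanatomical changes". The quantity of interest is therefore change within a person over about four years.

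Section 11.4.1 sets out the structural analysis: brain extraction, tissue segmentation with FAST, alignment of the grey matter maps to MNI space with FNIRT, and modulation by the Jacobian of the warp field. It then says that the modulation will "not include the affine part of the registration, which means that the data will be normalized for head size as a scaling effect". The maps are to be "smoothed with an isotropic Gaussian kernel with a standard deviation of 3 mm (FWHM: 8 mm"), and GLM and Bayesian models follow at regional and whole-brain level.

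The Protocol mentions no within-person registration, no transform shared by a participant's two scans, no skull-based scaling and no separate measure of whole-brain volume change.

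**The concern.** Leaving the affine part out of the modulation is a sensible correction when different people are compared once, because it removes differences in overall size. For one adult scanned twice there is no head-size difference to remove. What can change is the brain, and in this pipeline the skull is taken off before the grey matter maps are aligned. Unless it is constrained, the scaling then follows brain size. A brain that has become smaller overall is scaled up more at the second scan, and that extra scaling is not put back in the modulation.

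The part of atrophy that looks like a uniform rescaling is then treated as if it were head size. Within-person change would be understated, and any association of cognition or the microbiome with brain-wide loss would be attenuated. A region that shrinks less than the brain as a whole could appear stable, or even appear to grow. All 30 participants come from cohort 3, so no comparison of cohorts on MRI calls for this normalisation.

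The same paragraph also gives one smoothing kernel two incompatible widths.

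**Working it through.** The Protocol gives no numerical result for this measure, so there is no figure of its own to reproduce.

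**Inputs**
- Two scans per person, about four years apart, in 30 people (Section 5.2.2).
- Brain extraction before alignment, and modulation without the affine part (Section 11.4.1).
- Shared, uniform loss g: not in the documents; assumed 1% to 4% over four years, for illustration.
- Fraction f of the shared loss taken up by the second scan's affine: not in the documents; f = 1 is the upper bound, and f = 0 applies when both scans share one scaling.

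**Volume identity.** The volume factor from native to template space is the affine factor A times the non-linear Jacobian. With A left out of the modulation, reported grey matter = native grey matter × A. If the second scan's affine takes up a fraction f of the shared loss, its A exceeds the first by the factor 1/(1 − f·g). For a total regional loss r:

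reported loss = 1 − (1 − r)/(1 − f·g)

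**Full absorption (f = 1)**

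| True regional loss r | g = 1% | g = 2% | g = 4% |
|---|---|---|---|
| 2% | 1.01% | 0% | gain of 2.08% |
| 4% | 3.03% | 2.04% | 0% |
| 8% | 7.07% | 6.12% | 4.17% |

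For example, r = 4% and g = 2%: 1 − 0.96/0.98 = 2.04%, an understatement of (4 − 2.04)/4 = 49%. For r = 8% and g = 2%: 1 − 0.92/0.98 = 6.12%, an understatement of 23%. For r = 4% and g = 1%: 1 − 0.96/0.99 = 3.03%, an understatement of 24%.

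**Half absorption (f = 0.5), g = 2%.** The divisor is 1 − 0.01 = 0.99. A 4% loss is reported as 1 − 0.96/0.99 = 3.03%, and an 8% loss as 1 − 0.92/0.99 = 7.07%.

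**Purely uniform loss (r = g).** Losses of 1%, 2% and 4% are all reported as 0% under full absorption, as 0.50%, 1.01% and 2.04% under half absorption, and unchanged under one common scaling.

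**What is kept.** With a shared loss of 2% and a further regional loss of 5%, the true loss is 1 − 0.98 × 0.95 = 6.90%. Under full absorption the reported loss is 1 − 0.931/0.98 = 5.00%. The extra regional part survives in full; only the shared 2% is lost.

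**Kernel.** FWHM = 2√(2 ln 2) × SD = 2.3548 × SD. SD 3 mm gives FWHM 7.06 mm. FWHM 8 mm needs SD 8/2.3548 = 3.40 mm.

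**The case against.** The strongest reply is that the mechanism is inferred. Section 11.4.1 does not say how the affine is estimated, whether its scaling is constrained, or whether a participant's two scans share a transform. Section 11.4 refers to standard protocols, Section 5.2.2 adopts an external imaging design, and Section 19.1 promises detailed analysis plans. With a shared affine or skull-based scaling the problem would not arise. This stands as a limit on certainty, and it is why the loss is conditional on each scan getting its own affine. It does not clear the text: Section 11.4.1 does more than stay silent. It states a rule and its consequence, and that rule suits a single time point.

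A reader might infer three stronger things, and the documents support none of them.
- That brain-wide atrophy is removed entirely. Full absorption is only the upper bound: where ventricular fluid stays in the extracted volume, or the tissue thins with little change in brain outline, much of the loss is kept.
- That any link with atrophy disappears. Regional loss beyond the shared part is kept, and the structural hypothesis in Section 5.2.2 concerns medial temporal structures, which is a regional signal.
- That the signal is lost for good. The raw scans remain and can be reprocessed.

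It is also fair to say that the measure is optional, covers 30 of 360 participants, and appears neither among the Synopsis outcomes nor in the Section 3 outcome table. The kernel mismatch is a small, separate matter and lends no support to the scaling point.

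**Conclusion.** The point holds in a limited form. Section 11.4.1 prescribes a cross-sectional modulation rule for scans that are taken twice to measure within-person progression. Followed literally, with a separate unconstrained affine for each scan, it would attenuate the shared component of atrophy.

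The size rests on two quantities that the documents do not give: the shared loss, and the fraction that the affine absorbs. For a 4% regional loss, full absorption gives a reported loss of 3.0%, 2.0% or 0% at a shared loss of 1%, 2% or 4%. Half absorption at 2% gives about 3.0%. Apparent growth needs the shared loss taken up by the affine to exceed the region's own loss; the 2.08% gain in the table belongs to the extreme corner of the assumed range.

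The consequence is confined to the structural MRI change in an optional subgroup. The kernel inconsistency is certain but minor.

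**What to change.** In Section 11.4.1, state that a participant's two scans are analysed as a pair with one common scaling for both time points, either a shared affine-to-MNI transform or skull-constrained scaling. One way is a within-person template, with change taken from the within-person Jacobian so that brain-wide shrinkage is retained. Keep modulation without the affine part for cross-sectional analyses of the baseline scans only. State one smoothing kernel, either SD 3 mm (FWHM 7.06 mm) or FWHM 8 mm (SD 3.40 mm).

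The cost is a change of analysis wording and some extra processing time. No new scans or participants are needed.

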### 11.5 Blood sampling

A trained member of the Research Team will take the following samples at the QI CRF for which the participant will not be required to fast:-

- [figure not shown] 2 x 9.5ml (8 teaspoons) of blood will be taken for serum using serum separation tubes.

- [figure not shown] 2 x 10ml for plasma using EDTA tubes.

These will be taken at the Baseline Visit and Study Visits 2, 4, 6 & 8. Samples will be analysed at QIB.

- [figure not shown] 4ml of blood will be taken for a Full Blood Count (FBC) panel.

- [figure not shown] 5ml sample taken for Biochemistry panel.

- [figure not shown] 6ml sample taken for Troponin C.

These will be taken at Study Visits 1, 3, 5 and 7 and samples will be analysed at the NNUH.

Participants will provide 255ml of blood (51 teaspoons) in total over 4 years for the purpose of this study.

### 11.6 Health Questionnaires.

A Full Health Questionnaire (14 pages) requests information on the participant's diet and lifestyle. Participants will be asked to complete this questionnaire at their Baseline Visit at the QI CRF. Participants will be then requested to complete a Partial Health Questionnaire comprising of 5 pages at each of their follow-up visits (Study Visits 1 – 8) at the QI CRF.

### 11.7 Physical Measurement Collection (Height, Tanita Scales Measurement, BP (blood pressure) and Hand Grip Strength Measurements).

These measurements will be taken at the QIB CRF by a trained member of the Research Team at Study Visits 2, 4, 6 & 8. Height, BPs (taken once in each arm) and

hand grip strength measurements will be recorded manually on the Data Collection Case Report Form by the Study Researcher. The Tanita scale's body composition measurements will be taken with the participant's shoes and socks removed and by standing on the Tanita scales. The scales then provide an electronic print-out which the Study Researcher will add the participant's study identification number to. The print-out will then be photocopied and attached by stapler to the back of the DC CRF. The original print-out will then be stapled to the photocopied version.

### 11.8 Drop-off & collection of the stool collection pack.

The Baseline Visit stool collection pack will be given to the participant at the end of the Pre-Study Visit and the Study Researcher providing this will go through the collection instructions with the participant.

#### 11.8.1 Contents of stool collection pack

- Cool box.
- 3 x ice-packs measuring approx. 12cm by 13cm by 3cm.
- FaecesCatcher (device for collecting stool sample).
- Collection bags and gloves.
- Anaerogen sachet.
- Outer biohazard bag.
- Participant Sample Collection Log.

At the start of each of the follow-up visit appointments at the QI CRF (Baseline Visit - Study Visit 8), the Study Researcher will meet the participant and the cool box containing the stool sample and will be given to the experienced study Laboratory Technician for processing. The participant will be provided with their next collection pack containing all the stool collection equipment at the end of each visit appointment (apart from Study Visit 8). The Study Researcher will ensure that the participant understands the collection instructions at each visit.

## 12 SCREENING AND ELIGIBILITY ASSESSMENT

- Stream 1 participants from Primary Care will be sent the appropriate study pack by their GP who will have used the inclusion/exclusion search criteria to search for suitable participants.

- Stream 2 participants will be from the NNUH CSP.
- Stream 3 participants will be from the NSFT.

All participants will receive an initial Telephone Contact call by the Study Researcher. As part of this conversation, the Study Researcher will go through the PIS which lists all the inclusion/exclusion criteria.

At the Pre-Study Visit, all participants will then undergo the following Cognitive Test and associated questionnaire to assess final eligibility: -

1. Mini Addenbrooke's Cognitive Examination (Mini-ACE).
2. Cognitive Change Index (CCI).

## 13 SAMPLE HANDLING

### 13.1 Collection, Processing, Laboratory Analysis & Storage

Sample collection is fully described in Section 27. Only QIB-based researchers that are members of the Gut Microbes and Health strategic research programme that are directly involved with this study will access samples.

All samples will be anonymised and stored at -80°C until the end of the study. Any unused samples will be stored in the Norwich Biorepository and used in ethically approved studies in the future.

#### 13.1.1 Colon tissue Biopsy

##### **Why are we collecting these samples?**

Microbe populations that are specifically and intimately associated with the lining of the gut wall are ideally situated to influence the host and intestinal cells, but they can be underrepresented or absent in stool samples. For this reason, colon tissue samples are important to: 1) fully identify the microbes that are in most intimate contact with the host 2) identify and analyse how the cells within the tissue respond and react to these microbes and their products.

For colonoscopy biopsies, 6-8 pinch biopsies each measuring 3mm^3 will be taken from the large bowel during the CSP colonoscopy. These biopsies are taken to examine the microbiome that is adhering directly to the mucosal lining of the colon.

#### 13.1.1.1 Colon Tissue Biopsy Laboratory analyses

Tissue will be used immediately and/or preserved in long-term storage in the Norwich Biorepository. Fresh tissue will be placed directly into a plastic tube or in sterile media (e.g. RPMI, HBSS or media for *in vitro* organ culture [IVOC]) for immediate use in organ or cell culture systems, or for cell isolation and analysis. For organ culture, QIB has recently developed and optimised protocols for polarised IVOC and for isolating epithelial stem cell containing crypts from the intestinal epithelium dissected from biopsy samples. When placed into culture in media containing specific growth factors these stem cell-containing crypts faithfully generate intestinal epithelial organoids containing all of the different cell types found *in vivo*. This organ culture system provides a unique, powerful and accessible *in vitro* system to investigate microbe-host (epithelial) cell interactions in the gut. In addition, QIB is also developing microfluidics-based organ-on-a-chip technology with the aim of incorporating intact biopsy samples or cells derived from them (e.g. organoid cultures) into the chips. By linking in sequence gut chips with others containing brain-derived cells we will be able to investigate experimentally the pathways and mediators of gut-brain connectivity and the role gut microbes play in this process. This will be facilitated by incorporating in line monitoring (e.g. electrophysiology measurements) and sampling (of input and output channels) into the chip design. Other immediate means of processing tissue include those for (immuno) histology; isolating cells (e.g. immune and epithelial cells) for detailed characterisation (e.g. repertoire and subset identification and functional properties); proteins isolation/quantification (e.g. cytokines and other inflammatory or immunoregulatory proteins); and/or nucleic acids (DNA/RNA) extraction.

We will undertake targeted gene expression analysis from tissue biopsies. Total RNA will be extracted from fresh and frozen samples in commercially available RNALater solutions. RNALater product 'freezes' gene transcription and stabilises the RNA present so that it can be extracted at a later stage. Total RNA isolation will be performed using RNeasy kits (Qiagen) according the manufacturer's instructions following RNA later treatment; these are used routinely for the extraction and purification of RNA. Alternatively, RNA and proteins will be extracted from biopsy pre-treated with TRIzol® Reagent that allows the isolation of RNA, DNA, and protein from the same sample.

RNA extracted from the biopsy samples will be concentrated and the quality assessed using Agilent technologies lab-on-a-chip RNA 6000 nano assay. A selection

of genes, including but not limited to mucin, glycosyltransferases, tight junction proteins, serotonin transporter, tryptase, and protease-activated receptor 2 will be analysed by Real-Time RT-PCR. The methods are established in our laboratory at QIB and specific SOPs (Standard Operating Procedures) will be followed for the purpose of this study.

DNA will be extracted from tissue samples using the QIAamp DNA Mini Kit (Qiagen) according to the QIAamp DNA Mini Kit tissue protocol. DNA will be used to assess the composition of mucosa-associated microbiota and to determine selected genotypes considered relevant for the purposes of this study.

Genetic analyses performed during the study will not have any clinical relevance to participants or their relatives, therefore, participants will not receive any results of these tests.

For long term storage, biopsy samples will be preserved by, for example, snap freezing in liquid nitrogen (particularly useful for preserving RNA) and/or immersion in formalin (ideal for preserving tissue histology).

### 13.1.2 Stool sample

#### **Why are we collecting these samples?**

Gut microbes influence many important processes in the body including the digestion of food, programming of the immune system, and helping to prevent invasion of pathogenic microbes. Importantly, these microbes change during [39]ageing with these changes being associated with declining physical and mental health. Identifying microbes from stool samples allows us to determine: 1) which constituent members of the gut microbiome are changing and when: 2) what relationships there are between these changes and a deteriorating function of other organ systems (e.g. the brain, eyes, heart, liver, kidneys, bone and thyroid): 3) how different lifestyle and behavioural factors (e.g. medications) may contribute to changes in microbe populations.

Stool samples are taken to examine the microbiome content. Participants will produce their samples at home and bring it to the QIB within 24 hours of their scheduled study visit. They will also have the option of providing a sample within 24 hours after their scheduled study visit. Participants will be provided with their stool collection pack with full collection instructions (Annex 13). There will also be a AnaeroGen sachet for oxygen expulsion. Two days before the participant is due to produce their sample, participants will be requested to freeze their 3 ice-packs, so

they are frozen in good time. Participants will be requested to place their bagged stool sample between the ice-packs in order to preserve the integrity of the sample and the viability of as many microorganisms as possible until the sample is brought to QIB by the participant. The collection protocol has been developed according to International Human Microbiome Standards (IHMS) guidelines [39].

